#### Allocation concealment

Participants and the trial coordinator will not be blinded to their group allocation; however, the data collectors and the data analyst will be blinded. The codes will be broken following statistical analysis.

#### Sample size calculation

The Gpower3.1.9.2 software was used to conduct the sample size calculation. The sample size was estimated by power analysis using the Chinese high blood pressure-health literacy scale for the evaluation of HBP-HL as a primary outcome measure of the study. Cohen’s *d* and the effect sizes were calculated for between-group differences of means of the level of HBP-HL using an independent-groups pre-test and post-test design. From the evidence of our pilot study, the HBP-HL score of the intervention group was 32.09 ± 4.89 points, and that of the control group was 27.80 ± 4.78 points, which led to an estimate effect size as 0.405. The analysis, with a two-sided test using *β* = 0.2, *α* = 0.05, two sample *t-test*, and repeated ANOVA, requires a total sample size of 108 participants. Considering a 10% dropout rate, our final sample size comes to 120 participants (60 participants for both the intervention and control groups).

#### Intervention

Participants in each group will be divided into 3 teams of 15–20 people. Intensive intervention will be carried out for 9 months and twice a month in the first 2 months. During the other months, the intervention will be conducted once a month. Later, 3 months of follow-up will be conducted over telephone once a month and hypertension-related knowledge and videos (Putonghua and Huzhou dialect version) will be sent to the WeChat group once a week. Intermediary data will be collected at the 6th and 9th months to obtain timely feedback, to correct deviations, and to monitor and ensure the successful implementation of the intervention.

#### Intervention group

Interactive pictorial health education content (see Table 1) is drawn up according to 9 intervention functions of BCW theory that may stimulate behavioral change through several mechanisms of action.

**Table 1 Tab1:** Description of intervention content based on BCW theory

Intervention component	Intervention function	Mechanisms of action (COM)	Intervention time
**•**Explain the basic health knowledge of hypertension, help patients to acquire a correct concept of hypertension	Education	Psy C, Ref M	Week 1 of the first month
•Teach blood pressure monitoring skills, train patients to communicate with medical staff effectively	Training	Psy C, Phys C	Week 3 of the first month
•Recognize the hypertension complications, teach and encourage to set the goal of behavior change by themselves	Persuasion Realization	Psy C, Phys C, Ref M, Auto M, Soc O, Phys O	Week 1 of the second month
•Help patients understand the prevention measures of hypertension complications (medicine, diet)	Incentivisation	Ref M, Auto M	Week 3 of the second month
•Help patients understand the prevention of hypertension complications (exercise, weight management, sleep and psychological regulation)	Incentivisation	Ref M, Auto M	3th months
•Review the knowledge of complications of hypertension and feedback on behavior	Environment reconstructing	Soc O, Phys O, Auto M	4th months
•Review the preventive measures for complications of hypertension. Group instruction for patients with different health literacy problems	Environment reconstructing	Soc O, Phys O, Auto M	5th months
•Review blood pressure monitoring knowledge + peer knowledge sharing	Modeling	Auto M	6th months
•Review blood pressure monitoring knowledge + peer knowledge sharing	Modeling	Auto M	7th months
•Review blood pressure monitoring knowledge + peer knowledge sharing	Modeling	Auto M	8th months
•Review hypertension related knowledge	Education	Psy C, Ref M	9th months
• Follow-up with telephone and Wechat app	Education Environment reconstructing	Psy C, Ref M, Auto M, Soc O, Phys O	10th, 11th, and 12th months

A pictorial map will be used to visualize the content of health education and to guide the steps of the content, which is more acceptable for hypertensive patients with low HBP-HL. On the pictorial map, the size of which is 1 × 1.2 m, the text is written in a large, bold font to accommodate low functional health literacy levels and eyesight. The navigation arrows on the map indicate the steps of the intervention.

The educational content was developed by researchers based on a review of previous related research and programs and focused on medication, diet, exercise and weight management, sleep and psychological regulation, and knowledge of blood pressure monitoring and complications. Five experts evaluated the content of the health education program. The expert group consisted of cardiology, nursing, psychology, and pharmacology professors. The participants will use drawing implements to mark their progression through the educational content. The pictorial map will guide interactive discussions, which will facilitate the participants’ ability to acquire knowledge about hypertension. At the beginning of each intervention, educators will organize all participants to sit around the pictorial map in a U-shape. Each theme on the map comes with a set of questions that will be used as a framework by the facilitator to lead the discussion. In addition, the participants are encouraged to find the elements on the picture according to the theme and questions, guide the topic of development gradually through the corresponding content, and discuss with each other to deepen their understanding and memory. For example, the first question when using the map is to ask if they know the complications of hypertension. Ultimately, educators will guide everyone to review all the content discussed in the activity and answer the questions that they have not discussed yet to help participants sort out and consolidate the knowledge gained during the session.

#### Control group

The control group will only receive routine community lecture health education sessions, 9 months of intervention, and 3 months of follow-up.

### Outcomes and measuring instruments

#### Sociodemographic questionnaire

The questionnaire is a self-administered survey including age, gender, education, occupation, financial status, marital status, living condition, insurance status, smoking and alcohol status, history of hypertension, family history of hypertension, types of blood pressure medications, self-test blood pressure status, and complications.

#### Feasibility

We will calculate the proportion of participants completing the intervention. Attendance will be examined as the proportion of participants who attend 9/11 sessions and the average number of sessions attended. At the end of each intervention session, a 5-point Likert scale (not at all to very much) will be used to rate all participants to gauge their level of satisfaction with the project and their mental and social engagement. At the 3-month follow-up assessment, participants will indicate their level of interest in participating in the project in the future and whether they would recommend it to others.

#### Outcome evaluation scales

##### Chinese high blood pressure-health literacy scale (C-HBP-HLS) [30]

This scale is divided into 5 dimensions (Print Health Literacy, Medication Label, Understanding Ability, Newest Vital Sign Test, and Avoiding Food Allergy) consisting of 15 items, which was translated into Chinese and validated by Zhang Q et al. in 2016. According to the test of functional health literacy in adults (TOFHLA) scoring system, the final total score range is 0–60 points, and the higher the score is, the higher the HL level is. Furthermore, according to the TOFHLA classification criteria, the final score of the HBP-HL scale is divided into 3 grades: a total score < 32 points reflects a lack of HBP-HL; a total score ranging from 32 to 40 points indicates an intermediate level of HBP-HL; and a total score ≥ 40 points represents a high level of HBP-HL. The Cronbach’s *α* coefficient of the scale was 0.78, and the retest reliability was 0.96.

##### Hypertensive patients’ self-management behavior rating scale (HPSMBRS) [31]

This scale was developed and validated by F Zhao, Q et al. in 2012 and consists of 33 items in 6 dimensions (medication management, condition monitoring, diet management, exercise management, work and rest management, emotional management). The final total score ranges from 33 to 165 points. Higher scores reflect a better self-management behavior level in hypertensive patients. The Cronbach’s *α* coefficient of the scale was 0.914, and the content validity was 0.910.

##### Chinese SF-36 health survey [32]

The SF-36 has nine evaluation items, including physiological function, physiological function, physical pain, general health status, social function, emotional function, mental health, vitality, and one self-assessment of health changes. The total score is 145. The higher the score, the better the health-related quality of life.

##### Chronic disease self-management program (CDSMP) [33]

This program was developed by Lorig of Stanford University in 2001 during research on the self-management behavior of patients with chronic diseases. The scale includes 6 items using a 1–10 grade scoring method: level 1 means no confidence, level 10 means full confidence, the total average score of 6 items is scored, and the total score of the scale is 1–10, including 2 dimensions (symptom management self-efficacy, disease common management self-efficacy). The higher the score, the higher the level of self-efficacy. The total score of self-efficacy can be divided into three levels (low level: total score < 5, medium level: 5 ≤ total score < 7, high level: total score ≥ 7).

##### Perceived social support scale [34]

The scale is divided into 3 dimensions and 12 items, mainly including family support, friend support and other support. The scale adopts the scoring method from 1 to 7, and the higher the score is, the higher the social support level of participants.

### Clinical measurements

Blood pressure will be measured by the same surveyor with an Omron HEM-7211 electronic sphygmomanometer after the patient has rested quietly for at least 5 min. The measurement will be repeated at intervals of at least 5 min, and the average of the two readings will be recorded.

Anthropometric measurements, including height (cm), weight (kg), neck circumference (NC) (cm), waist circumference (WC) (cm), and hip circumference (cm), will be measured by researchers for all participants in lightweight clothing and bare feet. Body weight will be obtained using an Omron HBF-214 electronic scale, height will be reported by participants, and NC, WC, and hip circumference will be measured using a clinical tape measure. The parameters will be measured and recorded to the nearest 0.1 cm or 0.1 kg. Body mass index (BMI) is referred to as weight (kg)/height (m)^2^. According to the Working Group on Obesity in China, BMI is divided into normal weight (18.5 ≤ BMI < 24 kg/m^2^), overweight (24 ≤ BMI < 28 kg/m^2^), and obesity (BMI ≥ 28 kg/m^2^) [35]. NC is determined by measuring the horizontal circumference of the neck between the lower margin of the thyroid cartilage (Adam's apple) and the upper margin of the 7th cervical vertebra. WC is measured at the midpoint between the lateral anterior superior iliac spine and the lower border of the tenth rib. Using criteria from the WHO for the Chinese population, a WC ≥ 90 cm for men and ≥ 80 cm for women is considered abdominal obesity [36].

Measurements will be taken at baseline and at 6, 9, and 12 months from trial entry **(**the detailed timeline is shown in Table 2). To decrease the dropout rate, some retention strategies will be carried out: (1) collecting contact information of participants and their family members, (2) distributing a gift for every participant at each event, and (3) providing a quiet and comfortable environment for the intervention. In addition, the measurements will be collected by designated and appropriately trained and blinded assessors.

**Table 2 Tab2:** Summary of study assessments and timelines

Questionnaire items		Time point				
		Baseline T0	Randomized Allocation	The 6th month of intervention T1	The 9th month of intervention T2	Follow-up 3 months T3
Enrollment Eligibility screening Informed consent Screening						
Primary outcomes	C-HBP-HLS	√		√	√	√
Secondary outcomes	CDSMP	√		√	√	√
	HPSMBRS	√		√	√	√
	Perceived social support scale	√		√	√	√
	Chinese SF-36 Health Survey	√		√	√	√
	SBP	√		√	√	√
	NBP	√		√	√	√
	BMI	√		√	√	√
	NC	√		√	√	√
	WC	√		√	√	√
	hip perimeter	√		√	√	√
Sociodemographic data		√				

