### Randomization and blinding

#### Sequence generation

After completing the screening of the two communities with similar size, educational background and economic income, randomization will be performed at the level of the community after recruitment is completed. One community will be randomized to receive the intervention, and the other community will be randomized to the control group by throwing dice. The randomization process will be completed by a third party unrelated to the study. Only after the subjects have completed the baseline data collection, the allocation personnel can inform the researchers of the allocation results.

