### Data management

Data from the two stages of the study will be stored in a password-protected computer folder in the researcher’s office, where no one else is allowed to enter. Postgraduate students will be responsible for collecting, coding, analyzing, and recording the data; however, the Supervising Committee composed of community health care providers who have no competing interests with the sponsor and who will monitor the whole process. Only the research team will have access to the data.

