### Quality control

In collaboration with community health care providers before the trial entry, health care providers in each community are responsible for monitoring patient recruitment, consent, and collection of measurements. All researchers will be trained uniformly. To prevent bias, the data will be collected with unified measurements and analytical instruments by designated personnel (not the researcher himself) who are not clearly conducting the grouping. As soon as a questionnaire is completed, it will be strictly screened, and if there is any missing data, it will be completed in time. All data collection will be completed, encoded, and inputted by two people, and questionnaires with obvious errors will be removed. Epidata3.1 will be used to establish the database, randomly check and review it at a rate of 10%, and detect errors and correct them in a timely manner.

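### Assessor blinding is asserted, but the article is inconsistent about who takes the measurements, and one community per arm leaves the blinding fragile

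*Protocol article*

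**What the plan says.** Three places in the protocol article promise blinded collection. Allocation concealment states that "the data collectors and the data analyst will be blinded". The end of Clinical measurements states that "the measurements will be collected by designated and appropriately trained and blinded assessors". Quality control adds that data will be gathered by designated people other than the researcher, who are apparently meant to be unaware of the grouping.

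Other statements bear on the same staff:

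- **Sequence generation:** once baseline data are complete, "the allocation personnel can inform the researchers of the allocation results".
- **Clinical measurements, on height, weight and circumferences:** these "will be measured by researchers for all participants in lightweight clothing and bare feet".
- **Clinical measurements, on blood pressure:** "Blood pressure will be measured by the same surveyor", with no word on that person's blinding.
- **Quality control:** "health care providers in each community are responsible for monitoring patient recruitment, consent, and collection of measurements".
- **Data management:** "Postgraduate students will be responsible for collecting, coding, analyzing, and recording the data".
- **Allocation concealment:** "Participants and the trial coordinator will not be blinded to their group allocation".

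Setting and Sequence generation assign one community to each arm.

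**The concern.** Within one section, anthropometry is given both to blinded assessors and to researchers, and researchers are the people who learn the allocation. A reader cannot tell which statement governs. Circumferences taken with a hand tape leave some room for an observer's expectations, and BMI, neck, waist and hip circumference are listed as secondary outcomes at every post-baseline visit.

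The design adds a second difficulty. With whole communities as arms, knowledge about one participant transfers to everyone in the trial, so assessor blinding needs more protection than in an individually randomised trial. The article makes a positive claim of blinding without saying how it is kept under this design. If the claim passes unchanged into the trial report, readers will credit the results with protection against detection bias that the described procedures do not secure.

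**Working it through.** No alpha, power or sample size figure is involved. The check sets the statements side by side and counts what they affect.

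**1. When the risk starts.** Sequence generation releases the allocation only after baseline. Baseline (T0) is therefore unaffected. The exposed visits are T1, T2 and T3 (months 6, 9 and 12).

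**2. Who takes each outcome in Table 2.**

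| Outcome | Specific statement on who takes it | Conflict with the general promise of blinded assessors |
|---|---|---|
| BMI, neck, waist, hip (4 rows) | Researchers | Yes: the same noun as for those told the allocation |
| Blood pressure (2 rows) | One surveyor, blinding not mentioned | None stated |
| C-HBP-HLS, CDSMP, HPSMBRS, social support, SF-36 (5 rows) | None; mode of administration not given | None stated |

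Table 2 lists 1 primary and 10 secondary outcomes, 11 in all (4 + 2 + 5 = 11). The direct conflict covers 4 of 11, all secondary. For BMI it concerns weight more than height, because the section also says participants report their own height.

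**3. Who else is close to the measurements.** Each community's providers monitor collection. The Discussion hypothesises better communication skills and satisfaction among providers in the intervention group than among control providers. It is a reasonable inference, though not stated, that providers will know their own arm.

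**4. Collection and analysis.** Data management gives both tasks to postgraduate students. If both roles are blinded, as Allocation concealment says, there is no contradiction. The consequence is a dependence: a student who learned the arm while collecting would carry that knowledge into the analysis.

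**5. What one disclosure reveals.** There is one community per arm and 60 participants in each, so 60 + 60 = 120. Community determines arm exactly. For an assessor who knows participants' communities and knows that allocation was by community, learning the arm of one person gives the arm of 120 of 120. Under individual randomisation the same remark would reveal 1 of 120. Over three post-baseline visits, up to 120 × 3 = 360 participant assessments are exposed before dropout. This counts what a disclosure would reach; it does not estimate how likely a disclosure is or how much bias would follow.

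**The case against.** The strongest reply is that the article uses the word researchers loosely, for those who recruit, screen and measure alike. On that view, three specific statements (blinded collectors, blinded assessors, collectors other than the researcher) should govern one loose noun. Nothing shows that the people told the allocation are the people holding the tape. This stands as far as it goes: a reader might infer an established overlap, and the documents do not establish one. It does not remove the conflict, because the article leaves the reader to guess which statement prevails.

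A reader might also infer that blinding is impossible here. It is not. Community reveals arm only to someone who knows which community received the program, and an outside assessor could remain unaware. Controls also attend sessions, so a remark about attending would not identify the arm; the content would have to be described.

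A third tempting inference is that unblinded staff collect the primary outcome. No statement says so. The article gives no mode of administration for the C-HBP-HLS or the other scales; only the sociodemographic form is called self-administered. Blood pressure is taken by a surveyor with an electronic device.

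Monitoring by providers is oversight, and no statement has them administering or scoring anything. Finally, Strengths and limitations already concedes that the trial is not double-blind and has only two communities. That is partial disclosure, since it does not tell the reader that outcome assessment itself may be unblinded. Operational detail can be left to a full protocol; contradictory statements within the article cannot be excused in that way.

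**Conclusion.** The concern holds as an inconsistency in the text and a blinding claim that is fragile as written. The direct conflict is confined to 4 of 11 listed outcomes, at the three post-baseline visits. The structural weakness is wider: one disclosure can reveal all 120 allocations to an assessor who knows the communities. That conclusion rests on two things in the article (one community per arm, unblinded participants) and on the assumption that assessors know which community a participant comes from. The inference that providers know their arm strengthens the concern but is not needed for it.

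The documents do not show that unblinding takes place, and they do not support a figure for the resulting bias. The point warrants correction because the report would otherwise claim protection that is not secured, and because the correction is cheap.

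**What to change.** 1. Reconcile Sequence generation, Allocation concealment, Clinical measurements, Data management and Quality control, so that each outcome has a named role that measures it and a stated position on knowledge of the allocation.
2. In Clinical measurements, replace the assignment of anthropometry to researchers. State that all T1 to T3 outcomes, including anthropometry and blood pressure, are taken only by the already designated assessors, who neither deliver sessions nor receive the allocation.
3. In Quality control, limit community providers to oversight, with no part in administering or scoring outcomes.
4. Ask participants not to describe their sessions to assessors.
5. In Data management, make clear that students who collect or analyse data are among those not told the allocation.
6. If this cannot be assured with one community per arm, qualify or withdraw the blinded-assessor claim and add possible unblinded assessment to Strengths and limitations.

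Bringing both communities to common assessment days is not recommended: mixing the groups while the program is running risks contamination.

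The cost is revised wording, a short instruction to participants and firm allocation of tasks among the assessors already designated. The article's own route for amendments (Supervising Committee, then Ethics Committee) applies where the protocol is formally changed. The downside of item 6 is a less favourable statement on blinding.

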### Data management

Data from the two stages of the study will be stored in a password-protected computer folder in the researcher’s office, where no one else is allowed to enter. Postgraduate students will be responsible for collecting, coding, analyzing, and recording the data; however, the Supervising Committee composed of community health care providers who have no competing interests with the sponsor and who will monitor the whole process. Only the research team will have access to the data.

